## Results

This study was funded by the National Institute of Mental Health (R21 MH124794) in November 2020 with a start date of December 1, 2020, and an end date of October 31, 2022 (Multimedia Appendix 1). Recruitment and data collection began in April 2021, and 46 individuals were consented into the study through November 2021. Of note, the first study recruitment site (Covenant Health’s adult behavioral health inpatient unit) was unexpectedly closed on November 15, 2021, which resulted in a pause in recruitment while an alternative site was identified. As of February 2022, a new recruitment site has provided preliminary approval to restart study data collection, which began in June 2022. Data collection is anticipated to be completed by winter 2023.

## Discussion

### Expected Implications and Conclusions

Although suicide research has proliferated in the past 50 years, this work has not moved the needle substantively on suicide prevention, primarily because of a focus on static, between-person risk factors (*who* is at risk) rather than modifiable, within-person risk factors (*when* or *why* is a particular person at risk). Major suicide theories have proposed key drivers of STB, but very little research has directly compared the relevance of constructs across theories or tested whether these risk factors are related to dynamic fluctuations in suicide risk. In addition, empirical research on hypothesized cognitive and physiological contributors to suicide risk has been limited by an inability to measure these phenomena as they occur and change in daily life.

This study aims to address limitations in the research on SI and behavior in several ways. First, by examining between- and within-person experiences of a multitude of conceptually derived negative affective experiences, the results will clarify whether these are, in fact, uniquely and differentially related to suicide outcomes or whether they are more appropriately construed as indicators of a single latent construct, such as psychache. The results will thus clarify the utility of existing theories in which fine-grained, nuanced distinctions among risk factors may (or may not) map onto experiences that people with STB themselves discriminate among in daily life. Second, by using baseline and ambulatory measures of sleep disturbance and impaired inhibitory control, the results will clarify whether these serve as more stable or trait-like indicators of risk or whether fluctuations in these experiences relate to changes in risk over time. The results will inform the development of interventions designed to modify these risk factors in their most relevant contexts to decrease the odds of suicide among those at high risk.

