### Negative Affective Experiences

Shneidman [10] argued that suicide is fundamentally rooted in unbearable psychache, “hurt, anguish, soreness, aching, psychological pain.” Psychological pain is robustly associated with suicide, whether because of psychiatric disorders [18], stressful life events [19], or physical pain or illness [20,21]. Nonetheless, modern suicide theories differ in the relative importance of negative affective experiences as they relate to suicide. For example, the Interpersonal-Psychological Theory [12,22] focuses on interpersonal facets of pain, namely perceived burdensomeness and thwarted belongingness [23]. The Three-Step Theory formulated by Klonsky [9] takes a broader view of pain as a prerequisite for SI, positing connectedness as a protective factor against severe SI in the context of pain. Both the Three-Step Theory and the hopelessness model described by Beck [11] emphasize hopelessness regarding the likelihood of negative affective experiences improving over time as a key predictor of SI. The Integrated Motivational-Volitional model described by O’Connor [13] argues that SI is prompted by feelings of defeat (consistent with the view expressed by Baumeister [24] of suicide as escape from aversive self-awareness) and entrapment.

Although these models indicate multiple nuanced facets of negative affective experiences, it is unclear whether people experiencing suicidality differentiate these facets and whether they have differential predictive power. Recent network analyses suggest that many of these negative affective experiences cluster together among individuals [25]. However, to date, these studies have not conducted analyses of how these negative affective experiences covary over time within individuals or how they differentially predict outcomes. We aim to test the coherence of negative affective experiences to determine whether these are, in fact, differentially related to SI or whether they are more accurately conceptualized as indicators of the broader construct of emotional pain (eg, psychache).

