#### Data Analysis Plan

Before conducting analyses, we will clean and check data for errors, address outliers, ensure that statistical assumptions for analyses have been met, and examine potential confounders to include in subsequent analyses as warranted. Variables that may exhibit skewness (eg, number of lifetime episodes of NSSI) will be examined for skewness and kurtosis and, if necessary, either rank transformed or log transformed. We will include the effect of time (196 prompts over 28 days) to account for habituation and examine potential nonlinear effects of, for instance, age. Most analyses will use time-series (dynamic) structural equation modeling [98,99], which uses Bayesian estimation, conducted with MPlus statistical software (Muthén & Muthén) [99]. Dynamic structural equation modeling is robust with regard to high rates of missing data, zero-inflated categorical variables, and variable time intervals among observations, all of which are common in EMA with these types of data, and allows for latent decomposition of constructs into their constituent between- and within-person components [98]. Dynamic structural equation modeling also facilitates within-person lagged analyses to examine prospective relationships between time *t* predictors and time *t*+1 outcomes; by controlling for autoregressive effects over time, these methods can model within-person change in constructs over time.

For H1a, we will examine whether within-person changes in negative affective experiences precede proximal within-person changes in SI using 2-level random slope models. Each of 7 momentary negative affective experiences reported at time *t* will be regressed on itself at time *t–*1, producing a measure of residualized change in each negative affective experience. Momentary SI reported at time *t* will be regressed on itself at time *t–*1, as well as the 7 negative affective experience change indicators, yielding an estimate of the within-person effect of changes in all negative affective experiences on subsequent within-person changes in SI, controlling for autoregression. For H1b, we will examine the within- and between-person factor structures of the 7 negative affective experiences using multilevel exploratory factor analysis [100]. Using established best practices, we will identify the most appropriate structure and use these within-person factors to predict changes in SI over time, similar to the procedures used for H1a.

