With respect to the criteria used for statistical inferences, these will vary by model and hypothesis. For logistic regression analyses (H2a), 2-tailed *P* values <.05 will be used as our criteria to make inferences. For dynamic structural equation models (H1a, H1b, H2b, H3a, H3b, and H3c), which use Bayesian estimation, 95% credibility intervals will be used; those intervals that do not include 0 will be evidence of a statistically significant effect. For multilevel exploratory factor analysis (H1b), we will examine unrestricted models with 1 to 7 factors at the within- and between-person levels, consistent with the components of the negative affective experiences construct. We will determine the most appropriate model fit based on an examination of model fit indices [101] as well as eigenvalues.

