Despite these limitations, the study has numerous strengths. Data will be collected from a population known to be at exceptionally high risk for STB and for whom prior research has been limited by practical challenges involved in collecting data from inpatient psychiatric settings. This particular sample will be drawn from a high-need region where mental health care access is limited, facilitating understanding of risk factors for suicide in an underserved community where mobile interventions may be particularly critical to ameliorate suicide risk. Using a transtheoretical approach to understanding the transition from suicidal thoughts to behaviors, this study will facilitate direct comparison of key hypothesized risk factors as potential real-world contributors to suicide, moving forward both theoretical and empirical understanding of these phenomena. Furthermore, data collection will span a number of methodological approaches, including self-reports, interviewer ratings, behavioral measures, and ambulatory physiological readings, facilitating multi-trait, multi-method examination of STB risk. Finally, and most importantly, the intensive longitudinal design provides a novel opportunity to understand within-person changes in STB risk over time in contrast to prior work that has focused on between-person characteristics that relate to historical experiences of STB.

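### The stated H1a and H1b criteria cannot show whether the seven affective experiences predict suicidal ideation differently, which the article says the study will determine

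*Protocol article*

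**What the plan says.** The Introduction (Negative Affective Experiences) names two open questions about the facets: "whether people experiencing suicidality differentiate these facets and whether they have differential predictive power". It then makes one test serve both: "We aim to test the coherence of negative affective experiences to determine whether these are, in fact, differentially related to SI", the alternative being that they indicate a broader construct of emotional pain. The Discussion (Expected Implications and Conclusions) repeats the choice as the first contribution: "the results will clarify whether these are, in fact, uniquely and differentially related to suicide outcomes". The alternative offered there is again one underlying psychache factor.

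The Data Analysis Plan supplies two pieces.

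- **H1a.** SI is regressed on its own lag and on change indicators for all seven experiences in one two-level model. The criterion is whether each 95% credibility interval excludes 0.
- **H1b.** A multilevel exploratory factor analysis is run on the seven experiences, considering 1 to 7 factors. The criterion is: "We will determine the most appropriate model fit based on an examination of model fit indices", together with eigenvalues. SI comes in only afterwards: "we will identify the most appropriate structure and use these within-person factors to predict changes in SI over time".

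No stated criterion compares the seven slopes with one another, compares the seven-predictor model with the factor model, or tests experience-specific effects beyond the factor.

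**The concern.** Whether seven variables share a factor is a question about their mutual covariance. Whether they predict SI differently is a question about their relation to a variable outside that analysis. The answers can combine in any way: one dominant factor can coexist with one experience's specific part driving SI, and two factors can coexist with equal prediction. Presenting them as alternatives, and settling the structure without SI, leaves half of the question without a criterion.

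The H1a rule does not fill that gap. One interval that excludes 0 beside another that includes it does not show that the two slopes differ. At stake is the theoretical conclusion: whether the fine distinctions drawn by competing suicide theories matter for predicting SI.

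**Working it through.** The plan states no figure for this point, so there is none to reproduce. The check follows each rule and then illustrates it.

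**Inputs.** From Power Analyses and Sample Size Considerations: n = 100 participants, and 112 prompts each (4 × 28 = 112; 112/196 = 57.1%). Assumed: seven standardized indicators with a common loading λ of 0.6, 0.7 or 0.8, and SI residual SD 1. Least squares on person-centred data replaces the planned dynamic model, without autoregression or random slopes. There were 400 replicates per scenario, and the factor rule was one eigenvalue above 1.

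**Step 1: what the factor rule sees.** With equal loadings the first eigenvalue is 1 + 6λ² and the rest are 1 − λ². For λ = 0.7 this gives 1 + 6 × 0.49 = 3.94 and 0.51. No SI slope appears in either expression, so the structural choice is the same whatever the slopes are.

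**Step 2: simulation.** Where a cell has three values, they are for λ = 0.6 / 0.7 / 0.8.

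| True state | One factor chosen | Mixed intervals | Joint 6-df contrast rejects |
|---|---|---|---|
| One factor, all slopes 0.02 | 100% | 99.8 / 98.8 / 98.3% | 3.8 / 4.3 / 5.8% |
| One factor, all slopes 0.03 | 100% | 92.0 / 97.8 / 99.8% | 5.0 / 6.3 / 5.3% |
| One factor, all slopes 0.05 | 100% | 3.3 / 8.3 / 47.0% | 6.3 / 2.5 / 4.0% |
| One factor, one slope 0.14 or 0.21, other six 0 | 100% | 100% | 100% |
| Two factors (λ = 0.7), all slopes 0.03 | 0% | 94.5% | 3.3% |

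*Mixed* means that some of the seven intervals exclude 0 and some do not. The factor verdict is unrelated to differential prediction in both directions (rows 1 to 4 against row 5). A mixed pattern arises almost always with equal small slopes and always with one dominant slope, so by itself it does not separate the two. The contrast does.

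**Step 3: the scale of the slopes.** If SI depends only on the factor, with effect b, each partial slope is b × (λ/θ)/(1 + 7λ²/θ), where θ = 1 − λ². For λ = 0.7 and b = 0.3: 0.3 × 1.373/7.725 = 0.053. For b = 0.1 and 0.2 it is 0.018 and 0.036. The slopes of 0.02 to 0.05 in Step 2 therefore correspond to factor effects of roughly 0.1 to 0.3.

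**Step 4: what the contrast can detect.** If one slope exceeds the other six by d, the noncentrality is d² × 100 × 111 × θ × 6/7 on 6 df (critical value 12.59). For λ = 0.7 and d = 0.05: 0.0025 × 11,100 × 0.51 × 0.857 = 12.1, power 74% (85% at λ = 0.6, 56% at λ = 0.8). At d = 0.03 power is 37 / 29 / 21%; at d = 0.1 it is above 99%. Random slopes would lower these figures.

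**The case against.** The strongest reply is that the formal hypotheses are tested as written. H1a says each experience precedes increases in SI; H1b says one construct underlies them and predicts SI. Neither asserts that slopes differ, and each has a matching analysis. That stands, but the Introduction states differential relation to SI as an aim, so it is more than discussion wording.

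A reader might infer that the plan is blind to one experience driving SI. It is not. H1a enters all seven indicators jointly and is run whatever structure H1b selects. In the one-dominant-slope scenarios an average of only about 1.3 of seven intervals excluded 0, so the driver would stand out. What is missing is a criterion for calling it different from the rest.

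A reader might also infer that the investigators will rank theories or choose intervention targets by which intervals exclude 0. The article does not say so. The interpersonal-intervention remark in Dissemination Plan and Future Directions is a conditional example. The statement in Strengths and Limitations that "this study will facilitate direct comparison of key hypothesized risk factors" belongs to a sentence about the transition from suicidal thoughts to behaviors, not about the seven experiences predicting SI.

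The article is condensed, and the preregistration, which is not shown, could contain a contrast. However, the Data Analysis Plan sets out the inference criteria for H1a and H1b by name, and following them does not answer the stated question.

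The simulation is simplified. The 100% one-factor rate follows from generating one factor, the eigenvalue cutoff is an assumption because the plan gives none, and the mixed-pattern rate is largely a matter of power. The argument about the rules needs none of these figures.

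**Conclusion.** The point holds in this limited form. As written, the H1b choice of structure carries no information on differential prediction of SI, and H1a addresses unique but not differential relations. The stated criteria therefore cannot deliver the either/or answer in the Introduction and Discussion. Both alternatives can be true at once.

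The size is conditional on the assumed loadings, slopes and simplified model. With equal slopes of 0.02 to 0.03, a mixed pattern appears in 92% to 99.8% of one-factor runs; at 0.05 it falls to 3% to 47%. The risk of misreading is thus greatest when effects are small. H1a and H1b remain estimable and testable. What lacks support is the claim about differential relation.

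**What to change.** 1. Using the planned H1a and H1b models, prespecify one joint contrast of the seven standardized within-person slopes against the pattern implied by the selected factor. Equivalently, compare the factor-only SI model with one that adds experience-specific paths, one of them fixed for identification if a single factor is selected. Simple equality of slopes is the right null only if the loadings are equal.
2. Report factor structure and differential prediction as two separate conclusions.
3. Claim differential relation only from that contrast, not from which separate intervals exclude 0. If it is not clear, report differential prediction as unresolved; a contrast that does not reject is not evidence of equal prediction.
4. If a margin for negligible differences is wanted, justify it on the scale of the partial slopes. The 0.1 in the power section is a detectable effect from a logistic simulation and is nearly twice the 0.053 in Step 3 (0.1/0.053 = 1.9).

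Alternatively, limit the wording in Negative Affective Experiences and in Expected Implications and Conclusions to factor structure.

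The cost is one extra contrast or model and some wording, with no additional data to collect. The downside is that some theory comparisons may be inconclusive: Step 4 gives only 21% to 37% power for a slope difference of 0.03.

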### Methodological and Other Considerations

The primary methodological decisions in study design were with respect to the inclusion criteria, intensity of follow-up data collection methods, and level of monitoring and responsivity to indicators of suicide risk during follow-up.

First, we considered whether to limit the sample further (eg, individuals with recent SA) or whether to expand the inclusion criteria to include anyone receiving inpatient psychiatric care, regardless of recent STB. Individuals with a history of SA are at higher risk of later suicidal behavior than individuals with SI only [102], which would increase the odds of suicidal behavior during the follow-up period and plausibly increase statistical power. However, we felt that further restriction of the inclusion criteria would be likely to slow the speed of recruitment, a significant concern for a grant-funded study with a 2-year timeline. Recruiting a more heterogeneous sample will also allow us to examine the generalizability of predictors across a more diverse patient population. By contrast, expanding eligibility to all individuals receiving inpatient psychiatric care would likely reduce the odds of suicidal behavior over follow-up compared with individuals with recent STB [4].

Second, we considered the significant trade-offs between level of detail and frequency of follow-up assessments with the need to reduce participant burden (and, relatedly, the odds of attrition from the study). Prior research has shown that a greater number of surveys per day [103] and a greater number of items per survey [104] predict lower compliance with momentary assessment (EMA) research, which then affects the ability to adequately capture outcomes of interest (STB) during the EMA period. In addition, asking follow-up questions about the nuances of STB based upon *yes* responses during the EMA may increase the odds of participants choosing to deny these experiences that do occur to avoid additional follow-up questions, which take time and may be sensitive in nature. The duration and frequency of assessments chosen for this study were based on prior research suggesting that these parameters were feasible for the population of interest [105]. Finally, the 4- and 8-week follow-up interviews were added to the study protocol in response to grant reviewer feedback as a check against missed STB that were not captured during the EMA to increase statistical power for between-person models.

Finally, intensive longitudinal studies examining suicide risk and related constructs vary in the strategies used to monitor incoming data and to respond to indicators of elevated suicide risk [106]. These decisions often involve trade-offs of study investigator and staff time, guarantees of anonymity for participants, balancing participant safety with the risks involved in interventions by outside parties, avoidance of unintentional reinforcement of STB through study staff contact, and the goals of observational versus intervention-based research. Although we considered real-time monitoring of participants’ full range of EMA responses concerning suicide risk factors and contacting participants on the basis of these responses, we ultimately determined that this was scientifically unjustified because we do not know precisely what level of SI or other risk factors are related to imminent (proximal) risk for suicide. Follow-up with participants during the EMA protocol was limited to disclosures of suicidal *behaviors* only, following the aforementioned procedures.

However, we did make several choices across the study to promote truthful responding on suicide risk indicators by participants to ensure that they had adequate access to safety planning and other crisis resources and to avoid development of an intervention study when the study aims were exclusively observational. First, participants will be informed repeatedly at baseline that the study involves many assessments of STB and that many of these experiences will not lead to violations of their confidentiality. Participants will be informed that the confidentiality of information provided during the study will only be broken if the participant indicates imminent (within 1-2 days) desire, intent, and plans to attempt suicide and the research team member is not able to develop a safety plan with the participant to address this risk. Second, crisis hotline information and local, national, and web-based resources related to self-harm and suicide will be provided to participants at the baseline session, at which time all participants will be offered the opportunity to complete a suicide safety plan with the research team; if a safety plan is created, it will be given to the participant to keep and a copy will be retained by the research team. Furthermore, at the start of each EMA survey, participants will be offered live links to call or text 24/7 crisis hotlines, alongside a reminder that responses will not be monitored in real time; the same message will be displayed on the final page of each EMA survey. Each intervening page of questions will have a link at the bottom of the page that opens a full list of resources in a separate web browser if needed. Thus, participation in the research study will involve greater-than-usual exposure to, and reminders of, available crisis supports but will not involve routine additional intervention by the research team based on SI or related experiences.

